#### Participant timeline {13}

Figure 3 shows the *MyKid’sNutrition* RCT study schedule of enrolment, interventions, and assessments (according to SPIRIT guidelines; Supplementary Material 2).

**Fig. 3 Fig3:**
[figure not shown]
*MyKid’sNutrition* RCT study schedule of enrolment, interventions, and assessments (according to SPIRIT guidelines; Supplementary Material 2)

#### Sample size {14}

To estimate the sample size, we performed a statistical power analysis based on previous studies [24] and considering an alpha equal to 0.05 and a power of 0.80 with an effect size of 0.5 using G*Power 3.1.9.7. Accordingly, the sample size was estimated as 102 participants (51 mother–child pairs in each group). Finally, considering a dropout rate of 14%, the total sample size was calculated as 116 people.

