### Trial design {8}

We designed a two-arm RCT to evaluate the efficacy of the *MyKid’sNutrition* app. Following a baseline evaluation, children and their mothers will be randomly allocated to either the experimental group, *MyKid’sNutrition* app in addition to treatment as usual (TAU), or TAU alone as the control group. The patient allocation ratio will be 1:1. Figure 1 represents the *MyKid’sNutrition* RCT flowchart.

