### Statistical methods

#### Statistical methods for primary and secondary outcomes {20a}

We will use descriptive statistics for summarizing and determining the sample’s characteristics and distribution among the patients. Frequencies and proportions will be used to summarize categorical data. Analyzing associations between qualitative data variables will be done using the chi-square (*χ*^2^) test or Fisher’s exact test, as appropriate. The unpaired *t*-test or Mann–Whitney *U* test will be used to analyze quantitative data between the two independent groups. The analyses will be adjusted for age, sex, and other baseline characteristics as covariates when needed. A 95% confidence interval will be provided for all comparative analyses, and statistical significance for main effects will be determined as 5%.

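### The 102-participant sample size reproduces only with a one-sided 5% test; for the two-sided 5% analysis that the article implies, an unadjusted t-test has about 70% power, not 80%

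*Protocol article*

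**What the plan says.** The Sample size section {14} of the protocol article gives its inputs as "considering an alpha equal to 0.05 and a power of 0.80 with an effect size of 0.5 using G*Power 3.1.9.7". From these, "the sample size was estimated as 102 participants (51 mother–child pairs in each group"). It then inflates for loss: "considering a dropout rate of 14%, the total sample size was calculated as 116 people". The section names neither the test nor the outcome to which the effect size belongs, and it does not say whether alpha is one- or two-sided.

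The Trial design section {8} fixes equal allocation: "The patient allocation ratio will be 1:1". The Statistical methods section {20a} compares quantitative outcomes with an unpaired t-test or a Mann–Whitney U test; in its words, the "test will be used to analyze quantitative data between the two independent groups". On inference it says: "A 95% confidence interval will be provided for all comparative analyses, and statistical significance for main effects will be determined as 5" per cent. Covariate adjustment is conditional: "The analyses will be adjusted for age, sex, and other baseline characteristics as covariates when needed". The Outcomes section {12} speaks of changes within groups and differences between them, and gives no direction.

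**The concern.** For a two-group comparison of means with a standardised effect of 0.5, alpha 0.05 and 80% power, the familiar two-sided answer is 64 per group. The article's 51 is well below that. The likely explanation is that the software was run with one tail, while the analysis section reads as two-sided.

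The stake is how the result is read. The article tells readers that the trial misses an effect of 0.5 one time in five. Under a two-sided unadjusted t-test it would miss it about three times in ten. A null result would then look like stronger evidence against the app than the design can supply. Leaving sidedness unstated also leaves room to choose it after the data are seen.

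**Working it through.** **Inputs.** Standardised effect d = 0.5, alpha 0.05, power 0.80, 51 per group, 14% dropout and 116 in total (all Sample size {14}); 1:1 allocation (Trial design {8}); unpaired t-test, 95% intervals and 5% significance (Statistical methods {20a}). Assumption: the effect size is Cohen's d for two independent means, since the article does not define it.

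**Formula.** With n per group, the t statistic has 2n − 2 degrees of freedom and noncentrality d × √(n/2). Power is the probability that this noncentral t exceeds the critical value (one-sided), or exceeds it in absolute value (two-sided). For two means, G*Power uses this exact calculation.

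**Step 1: reproduce the plan's figure.** At n = 51 the noncentrality is 0.5 × √25.5 = 2.525, with 100 degrees of freedom.

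| Test | Critical t | Power at 51 per group | Smallest n per group for 80% |
|---|---|---|---|
| One-sided 0.05 | 1.660 | 80.6% | 51 (50 gives 79.9%) |
| Two-sided 0.05 | 1.984 | 70.6% | 64 (63 gives 79.5%, 64 gives 80.1%) |

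The one-sided row matches the article exactly. A two-sided alpha of 0.10 also gives 51, because its critical value is the same.

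**Step 2: look for another route to 102.** None of these gives 102 in total:
- Mann–Whitney with normal data: 106 one-sided, 134 two-sided.
- Mann–Whitney with logistic data: 92 and 118.
- Mann–Whitney with Laplace data: 68 and 86.
- Mann–Whitney at its minimum efficiency: 118 and 148.
- Paired t-test: 27 and 34.
- Chi-square with w = 0.3: 88, 108 or 122 for 1, 2 or 3 degrees of freedom. With w = 0.5: 32, 39 or 44.
- Analysis of covariance with f = 0.25: 70.6% power at 102, so 102 is not its 80% answer.

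**Step 3: which sidedness does the analysis imply?** A two-sided 95% interval corresponds to a two-sided 5% test. A one-sided 5% test corresponds to a 90% interval. The article promises 95% intervals with a 5% level, frames the outcome without direction, and nowhere mentions a one-sided test.

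**Step 4: the dropout step.**
- 102 × 1.14 = 116.3, which is the stated 116.
- Keeping 102 after 14% loss needs 102 / 0.86 = 118.6, so 119.
- 116 × 0.86 = 99.8, about 50 per group; two-sided power is then 69.7%.
- 116 keeps 102 evaluable only if at most 14 are lost: 14 / 116 = 12.1%.
- With no loss at all (58 per group), two-sided power is 76.1%, still short of 80%.

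**Step 5: detectable effect.** The effect detectable with 80% two-sided power is d = 0.56 at 51 per group and d = 0.57 at 50 per group.

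**The case against.** **Sidedness is inferred.** Neither section writes it down. This stands: a reader might conclude that the article declares a two-sided test and then contradicts itself, and it does not go that far. The inference is still the ordinary one, and the text needs repair on either reading. If one-sided was meant, the sample size section must say so and the 95% intervals do not match it. If two-sided was meant, the 80% is wrong.

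**The 70% belongs to one analysis only.** A reader might infer that the trial's power is 70% whatever is done. The article does not support that. It allows covariate adjustment, which could raise power, and a Mann–Whitney test, which on normal data gives about 68.5% at 51 per group. But adjustment is planned only where needed, the baseline value of the outcome is not named as a covariate, and the sample size section does not rely on it.

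**Baseline adjustment restores 80%.** It is tempting to say this happens once the correlation between baseline and 3 months is high enough. The condition depends on which standard deviation defines d, and the article does not say. At 50 per group:
- If d is scaled by the final-value SD, adjustment multiplies the variance by 1 − r², and 80% needs r of at least about 0.47.
- If d is scaled by the change-score SD, which the Outcomes section's emphasis on change would suggest, the factor is (1 + r)/2, and 80% needs r of at most about 0.56.

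The two conditions run in opposite directions, and no correlation is given. No recovery claim can rest on this document.

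**The damage is limited.** This also stands. The estimate is not biased, the type I error of a two-sided 5% analysis is unaffected, and the confidence intervals will show the precision achieved. The dropout slip moves power by only 0.9 points (70.6% to 69.7%).

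**Conclusion.** The point holds as a misstated design property. The stated 102 fits only a one-sided 0.05 critical value, and no part of the article states or defends a one-sided test. Under the two-sided 5% analysis that the article implies, an unadjusted t-test falls about 9 points short of the claimed power. The chance of missing an effect of 0.5 is about 30% instead of 20%, and 128 evaluable participants would be needed where 102 are planned. The dropout error is a side note.

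This rests on three assumptions: the effect size is Cohen's d, the comparison is the unadjusted t-test, and the intended analysis is two-sided. It does not show that the investigators intend to test one-sided, nor that power would be 70% under a baseline-adjusted model.

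**What to change.** Keep 116 participants and replace the power statement with wording such as: *Two-sided alpha 0.05. With 116 randomised and 14% dropout (about 100 evaluable), an unadjusted t-test has about 70% power for d = 0.5 and 80% power for d = 0.57.*

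Correct the dropout step in the same paragraph, either by dividing by 1 − 0.14 or by stating that 116 tolerates about 12% loss. Do not add a claim that baseline adjustment restores 80% power, because the article gives neither the scale of d nor a correlation.

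The cost is the rewording of one paragraph and a less favourable power figure. No further participants are needed.

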#### Methods in analysis to handle protocol non-adherence and any statistical methods to handle missing data {20c}

Missing data will not be imputed. All available data will be used in the models.

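### The total of 116 does not keep 102 pairs at 14% dropout: about 100 would remain, and 116 covers about 12% (a minor arithmetic correction)

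*Protocol article*

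**What the plan says.** Sample size {14} of the protocol article gives the design inputs as "considering an alpha equal to 0.05 and a power of 0.80 with an effect size of 0.5". From these, "the sample size was estimated as 102 participants (51 mother–child pairs in each group"). The dropout step follows: "considering a dropout rate of 14%, the total sample size was calculated as 116 people". No inflation formula is printed. The Abstract repeats 116 as the number to be randomized in equal proportions, and Trial design {8} says "The patient allocation ratio will be 1:1".

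Outcomes {12} places the outcome measurements at baseline and after three months. The section on missing data, {20c}, says "Missing data will not be imputed" and adds that whatever data are available will enter the models.

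**The concern.** The section prints three linked figures: 102 evaluable, 14% dropout and 116 enrolled. In its ordinary sense a dropout rate applies to the people enrolled. On that reading the figures do not fit together, because losing 14% of 116 leaves fewer than 102.

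The power statement is attached to 51 pairs per group. Outcomes are measured only once after baseline and missing values are not imputed, so a pair that misses the three-month visit has no follow-up value for the between-group comparison. The number of completers is therefore the effective sample size. At stake is whether the stated enrolment supports the stated power at the plan's own dropout rate, and whether the dropout allowance is reported correctly.

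**Working it through.** **Inputs.** From Sample size {14}: alpha 0.05, power 0.80, effect size d = 0.5, evaluable N = 102 (51 per group), dropout 14%, total 116. From Trial design {8}: allocation 1:1. Sample size {14} does not say whether the test is one-sided or two-sided, so both were tried.

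**1. Reproducing the plan's total.**
- 102 × (1 + 0.14) = 116.28, which rounds to the printed 116.
- Equivalently, 116 − 102 = 14 extra participants; 14 / 102 = 13.7%, whereas 14 / 116 = 12.1%.

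**2. Inflation on the enrolled number.** N = 102 / (1 − 0.14) = 118.6, so 119. By arm, 51 / 0.86 = 59.3, so 60 per group and 120 in total. The result 118.6 does not round to 116.

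**3. What 116 delivers.**
- Expected completers at 14% dropout: 116 × 0.86 = 99.8, or 58 × 0.86 = 49.9 per group.
- Dropout that 116 can absorb while keeping 102: 1 − 102/116 = 12.1%.

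**4. Reproducing the base figure.** For a two-sample t-test with n per group, the noncentrality parameter is d × √(n/2), and power comes from the noncentral t distribution with 2n − 2 degrees of freedom. Solving for power 0.80 at d = 0.5:
- one-sided 0.05: n = 50.15, so 51 per group and 102 in total, which matches the plan;
- two-sided 0.05: n = 63.77, so 64 per group and 128 in total, which does not.

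**5. Power at the intended and the expected number of completers.**

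| Test at d = 0.5 | 51 per group | 50 per group | Difference |
|---|---|---|---|
| One-sided 0.05 | 80.6% | 79.9% | 0.7 points |
| Two-sided 0.05 | 70.6% | 69.7% | 0.9 points |

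At the unrounded 49.88 per group the values are 79.8% and 69.6%.

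**6. Shortfall against the unrounded requirement.** On the one-sided basis, 0.80 needs 2 × 50.15 = 100.3 pairs. The expected 99.8 is about half a pair below that. Rounding up to 51 per group had already created slack that absorbs nearly all of the loss.

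**The case against.** The strongest defence is that the slip has almost no consequence. On the test that reproduces 102, power at 50 per group is 0.799, which rounds to the stated 0.80; measured against the 0.80 target, the loss is 0.1 to 0.2 points. This stands, and it sets the size of the point.

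A second defence is that no formula is printed. If 14% is read as an allowance added on top of 102, the three figures agree to rounding. That is possible, but the text calls it a dropout rate, and the added-margin reading is the less natural one. If it was meant, the sentence still needs rewording, because a reader will take 14% of those enrolled.

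Third, {20c} says that all available data will be used, and the analysis section allows covariate adjustment when needed. Neither supplies a missing three-month value, though adjustment could offset a loss this small.

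Two stronger readings are tempting. A reader might infer that the dropout step leaves the trial materially underpowered; the table does not support that, since the step costs less than one point on either test. The low two-sided figures come from the base of 102, not from the dropout step. A reader might also infer that retention tracked against 14% would look on target while the required number is missed. The retention section, {18b}, describes calls, messages, reminders and appointment scheduling. It sets no numerical target and no monitoring against 14%, so that harm has no basis in the document.

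**Conclusion.** The sentence is wrong as written if 14% has its ordinary meaning as a share of those enrolled. At that rate 116 leaves about 100 pairs rather than 102, and 116 covers about 12% dropout rather than 14%. Dividing by 0.86 would have given 119, or 120 with equal arms: 3 or 4 more participants. That the plan multiplied by 1.14 is an inference from the match; the mismatch holds whatever formula was used, and no other section of the article repairs it.

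The effect is minor, under one point of power and essentially the stated 0.80 on the one-sided basis. The power figures assume an effect size of 0.5, a t-test, dropout equal in the two arms and analysis of completers only.

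The figure of 102 is taken here as the plan's own. Whether it is the right base is a separate question, since a two-sided 5% test would need 128. The dropout correction applies whichever base is used.

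**What to change.** Keep enrolment at 116 and correct the one sentence in Sample size {14}, in either of two ways:

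- state that 116 allows for about 12% dropout while retaining 102 pairs; or
- keep 14% and state that about 100 evaluable pairs (50 per group) are expected, with power quoted at 50 per group on the test actually intended.

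Make the change together with any restatement of the base figure of 102 for sidedness, because a new base requires the dropout step to be redone. For example, a two-sided base of 128 gives 128 / 0.86 = 148.8, so 149, or 150 with equal arms (64 / 0.86 = 74.4, so 75 per group).

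Taken alone, the correction costs one sentence and no additional participants. The only price is a slightly less favourable dropout allowance or evaluable number. Nothing in {18b} needs to change for this point.

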#### Recruitment {15}

All subjects will be selected from people referring to the pediatric outpatient clinics in Isfahan, Iran. We will reach out to participants who attend in-person visits. We will also use written advertising (flyers, brochures, etc.). All potential and interested volunteers will be referred to a coordinator who will determine if the individual meets the initial eligibility requirements. Finally, all eligible participants will sign a written informed consent and agree to participate in the study voluntarily.

### Assignment of interventions: allocation

#### Sequence generation {16a}

Following baseline assessment, all eligible participants will be randomized (1:1 ratio) to intervention or usual care groups. The process of random sequence generation and the allocation of participants to intervention conditions will be implemented on an online platform by an independent researcher not involved in the process of subject recruitment.

#### Concealment mechanism {16b}

Since the randomization process occurs using an online tool and by an independent researcher, the process is fully concealed from both study investigators and prospective participants until the study arm is assigned.

#### Implementation {16c}

A clinical research coordinator will enroll all participants and assign them into groups.

### Assignment of interventions: blinding

#### Who will be blinded {17a}

Due to the nature of the intervention, neither the research team nor the patients in both arms can be blinded to the patients’ allocation. However, the outcome assessment team, as well as those who are involved in data analysis and statistics will be blinded to the group allocations.

#### Procedure for unblinding if needed {17b}

The design is open-label with only outcome assessors being blinded so unblinding will not occur.

### Data collection and management

#### Plans for assessment and collection of outcomes {18a}

We will use a questionnaire to collect all participants’ sociodemographic and baseline information, including name, sex, age, contact information, family size and income, past medical history, phone number(s), education, and occupation. The research team will measure all children’s anthropometric indices and the presence of undernutrition will be assessed based on growth charts [6]. Using a questionnaire with confirmed psychometric properties, the mothers’ nutritional knowledge, attitude, and practice will be assessed [25]. All data will be collected in a uniform and reproducible manner by trained data collectors. The quality of the data will be supervised by the principal investigator.

#### Plans to promote participant retention and complete follow-up {18b}

The research team will provide periodic communications with participants via telephone and text message. Also, they will use methods to improve participant retention, such as reminders for using the application and scheduling appointments for post-intervention visit.

#### Data management {19}

To improve the quality and accuracy of data, all data will be entered twice and double-checked by two independent administrators. The data obtained in this study will be archived at Tabriz University of Medical Sciences, Iran. Access to this data will be limited to data administrators and statisticians. Each patient will be assigned a unique and confidential participant ID that is only accessible by the research team, and all personal data will be coded. We will separate patients’ personal information from the database containing their medical information.

#### Confidentiality {27}

Using a study identification code for each participant, the research data will be stored. The research team will have access to the key to the identification code list during the study, which will be documented and safeguarded by the principal investigator according to the research guidelines after the completion of the study. Personal details of the participants will not be reported in the publications.

#### Plans for collection, laboratory evaluation, and storage of biological specimens for genetic or molecular analysis in this trial/future use {33}

This is not applicable to the current study, since this trial does not involve collecting biological specimens for storage.

### Statistical methods

#### Statistical methods for primary and secondary outcomes {20a}

We will use descriptive statistics for summarizing and determining the sample’s characteristics and distribution among the patients. Frequencies and proportions will be used to summarize categorical data. Analyzing associations between qualitative data variables will be done using the chi-square (*χ*^2^) test or Fisher’s exact test, as appropriate. The unpaired *t*-test or Mann–Whitney *U* test will be used to analyze quantitative data between the two independent groups. The analyses will be adjusted for age, sex, and other baseline characteristics as covariates when needed. A 95% confidence interval will be provided for all comparative analyses, and statistical significance for main effects will be determined as 5%.

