#### Outcomes {12}

The outcomes of *MyKid’sNutrition* trial would be the change in the growth indicators and mothers’ nutritional knowledge, attitude and practice within the groups, and the differences between the groups. Weight for height and BMI for age *z*-scores, which are the growth indicators and mothers’ nutritional literacy, will be measured at baseline and after 3-month follow-up visits. Additionally, the participants’ demographic and socio-economic status will be measured.

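### The plan does not commit to adjusting each outcome for its own baseline value, and leaves whether and for what to adjust open until the data are seen

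*Protocol article*

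**What the plan says.** All statements below are from the protocol article.

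- **Test.** Under Statistical methods for primary and secondary outcomes {20a}, the unpaired t-test or Mann–Whitney U "test will be used to analyze quantitative data between the two independent groups". No other method is named for quantitative outcomes.
- **Adjustment.** The next sentence reads: "The analyses will be adjusted for age, sex, and other baseline characteristics as covariates when needed". No criterion for need, no closed list and no adjusted model follows. The section on missing data {20c} mentions models, but {20a} does not specify any.
- **Outcome.** Under Outcomes {12}, the outcomes "would be the change in the growth indicators and mothers’ nutritional knowledge, attitude and practice within the groups, and the differences between the groups". The growth z-scores and the mothers' nutritional literacy "will be measured at baseline and after 3-month follow-up visits".
- **Sample size.** Sample size {14} works "considering an alpha equal to 0.05 and a power of 0.80 with an effect size of 0.5" and arrives at 51 mother–child pairs per arm. It does not say which outcome the effect size refers to, whether it is scaled to the 3-month value or the change, or whether the test is one- or two-sided.

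**The concern.** The baseline value of an outcome is usually the most informative covariate a trial of this kind has, and here it is measured for every growth and questionnaire outcome. The plan names age and sex but not this value. Neither named test takes covariates, so the adjustment sentence must refer to some further analysis that is not identified. It is also not stated whether the 3-month value or the change goes into the named test.

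Two things are at stake. The first is precision: the analysis finally used may be less efficient than one available from the same data. The second is discretion: with no trigger and no closed list, the choice of whether to adjust, and for what, can be made after the results are visible.

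**Working it through.** **Inputs.** From Sample size {14}: alpha 0.05, power 0.80, effect size 0.5 (taken as Cohen's d), 51 per arm. From {20a}: 5% significance and 95% confidence intervals, read here as two-sided. Assumed, because the document does not give them: the correlation r between the baseline and 3-month values, and the SD on which d is scaled. Equal SDs at both times are also assumed.

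**Step 1. The plan's own figure.** An unadjusted two-sample t-test with d = 0.5, one-sided alpha 0.05 and power 0.80 needs 50.15, so 51 per arm, or 102: an exact match. The two-sided version needs 63.77, so 64 per arm, or 128. At 51 per arm, power is 80.6% one-sided and 70.6% two-sided. Sidedness is a separate matter. The step matters here only because it shows that the calculation rests on an unadjusted comparison.

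**Step 2. Variance of the treatment difference, relative to a comparison of 3-month values.**

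- 3-month value: 1
- Change score: 2(1 − r)
- ANCOVA on the baseline value: 1 − r²

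Since 1 − r² = (1 − r)(1 + r) and 1 + r < 2, ANCOVA has the smaller variance than the change score for any r below 1. It also has the smaller variance than the 3-month comparison for any r other than 0. The change score is worse than ignoring the baseline when 2(1 − r) > 1, that is, when r < 0.5.

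**Step 3. Two-sided power, 51 per arm, d = 0.5 on the 3-month SD.** Effective d is 0.5/√(variance factor).

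| r | 3-month value | Change score | ANCOVA |
|---|---|---|---|
| 0.3 | d 0.500, 71% | 0.5/√1.40 = 0.423, 56% | 0.5/√0.91 = 0.524, 75% |
| 0.5 | d 0.500, 71% | 0.5/√1.00 = 0.500, 71% | 0.5/√0.75 = 0.577, 82% |
| 0.7 | d 0.500, 71% | 0.5/√0.60 = 0.645, 90% | 0.5/√0.51 = 0.700, 94% |

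Pairs per arm for 80% two-sided power at r = 0.3, 0.5 and 0.7: 64 throughout for the 3-month value; 89, 64 and 39 for the change score; 59, 49 and 34 for ANCOVA.

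**Step 4. The same with d = 0.5 on the change SD.** The change score then has 71% power at every r. ANCOVA has effective d = 0.5 × √[2(1 − r)/(1 − r²)] = 0.5 × √[2/(1 + r)].

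- r = 0.3: d = 0.620, power 87%
- r = 0.5: d = 0.577, power 82%
- r = 0.7: d = 0.542, power 77%

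The ranking of ANCOVA over the change score does not depend on the scale of d. The size of the gain does.

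**Step 5. Type I error of an open rule.** Simulation under no effect: 40,000 trials per value of r, 51 per arm, nominal two-sided 5%, with the baseline outcome as the only covariate.

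| Rule | r = 0.5 | 0.7 | 0.8 | 0.9 |
|---|---|---|---|---|
| Smaller p of 3-month test and ANCOVA | 7.4% | 8.2% | 8.8% | 9.1% |
| Smaller p of change score and ANCOVA | 7.5% | 6.8% | 6.3% | 5.9% |
| Smallest p of all three | 9.8% | 10.1% | 10.1% | 10.1% |
| ANCOVA only if baseline imbalance p < 0.05, otherwise 3-month test | 4.4% | 3.6% | 3.0% | 2.3% |

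Each single analysis, fixed in advance, stayed near 5% (4.9% to 5.2%).

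**The case against.** **The baseline is not thrown away.** A reader might infer from the two named tests that the plan discards it. The document does not support that. Outcomes {12} frames the outcomes as change, and an unpaired t-test on change uses every baseline value. The open phrase about other baseline characteristics could also cover the baseline outcome. This objection stands; what remains is that the plan commits to neither.

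**It is detail for an analysis plan.** An article may leave the model and covariate list to a fuller document. That is fair for what is merely absent. But {20a} does not defer the choice: it states a rule, and the rule is conditional and open-ended. A later plan with fixed adjustment would have to override it.

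**Both analyses are unbiased.** Under randomisation this is true, so preferring ANCOVA is an efficiency argument and not the correction of a bias. It is still a better method at no extra data cost.

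**The error rate need not suffer.** If *when needed* means adjusting after a significant imbalance test, type I error falls below 5%. Inflation requires reporting the most favourable of several analyses, which the wording permits but does not plan. This stands as a limit on the claim.

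**The confidence interval.** It is tempting to say that Mann–Whitney contradicts the interval promised in {20a}. That section promises an interval for comparative analyses, not an adjusted difference, and a Mann–Whitney comparison can be reported with a Hodges–Lehmann shift and its interval. No contradiction is shown.

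**Conclusion.** The point holds in a limited form. The protocol article does not fix whether the 3-month value or the change is tested, does not commit to adjusting for the baseline value of the outcome, and leaves the use and content of adjustment open. A prespecified ANCOVA is more efficient than the change score at every r examined and on either scale for d. Against the change score at 51 per arm, the gain runs from 4 percentage points (r = 0.7, 94% against 90%) to 19 (r = 0.3, 75% against 56%) with d on the 3-month SD. With d on the change SD it runs from 6 (r = 0.7) to 16 or 17 (r = 0.3). These sizes rest on an assumed r and an assumed scale.

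For the same reason, one should not infer that adjustment would make up for a shortfall in the sample size. With d on the 3-month SD and r = 0.3, ANCOVA reaches only 75%; with d on the change SD and r = 0.7, only 77%. Nor does the wording by itself breach the 5% level: that happens only with selective reporting. This is an improvement the trial should make; it does not show that the planned comparison is invalid.

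**What to change.** In Statistical methods {20a}, replace the sentence naming the t-test and Mann–Whitney test and the adjustment sentence after it with text such as:

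*Each continuous outcome is analysed by a linear model (ANCOVA) of the 3-month value on randomised arm, the baseline value of the same outcome, child age and child sex. These covariates are fixed in advance and used regardless of observed imbalance. The adjusted mean difference with its two-sided 95% confidence interval is the reported effect. A Mann–Whitney comparison is a sensitivity analysis only.*

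This removes the *when needed* condition and the open list. If skewed residuals are a worry, name robust or bootstrap standard errors in the same place.

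The cost is wording only. The baseline and 3-month outcome values are already scheduled under Outcomes {12}, and age and sex are collected under Plans for assessment and collection of outcomes {18a}.
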